## Abstract

**Background:**

In our modern society, physical activity (PA) is decreasing and sedentary time (ST) is increasing, especially for children from disadvantaged neighborhoods. School-based interventions to promote PA and decrease ST are therefore required among this population in order to change children’s lifestyle habits. Moreover, attentional capacities and academic achievement can be enhanced by chronic PA during childhood. The relationships between these variables have been poorly studied with this population.

**Objective:**

The objective of this study is to present the rationale and methods for a randomized controlled trial among 6-10-year-old children with low socioeconomic status that will (1) evaluate the effectiveness of a school-based intervention designed to promote PA and reduce ST and (2) study the relationships between PA, ST, motor skills, attentional capacities, and academic achievement.

**Methods:**

A randomized controlled trial was conducted in 2 eligible primary schools. During academic year 2016-2017, 1 school was randomly assigned as the experiment one and the other was assigned as the control one. Five assessments times were used: baseline (T1 [November 2016] to T2 [June 2017]), follow-up (T3 [November 2017] to T4 [June 2018]), and final assessment (T5 [June 2019]). The school-based intervention included various components on different levels of the socioecological model: (1) curriculum-based program for children; (2) sensitization workshops and newsletters for parents; (3) training workshops for teachers; (4) environmental adaptation of playgrounds and reorganization of recess time; (5) time adaptation of lunch breaks; and (6) collaboration with political groups. PA, ST, motor skills, and attentional capacities were evaluated and academic achievement was recorded.

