### Study Design and Population

The study was designed as a randomized controlled trial with 2 arms. In a mid-sized city in the southern part of France, 2 primary schools located in the city’s disadvantaged neighborhood were invited to participate in the study. In France, neighborhoods are classified as disadvantaged on the criterion of income per inhabitant: this income is compared with the average income of the city and that of France. This defines the unfavorable social and economic conditions of the neighborhood and its inhabitants. For example, in the neighborhood considered in this study, the unemployment rate is the highest in the city (26% vs 18%) as well as the prevalence of social housing (49% vs 23%).

Both primary schools agreed to participate in the project. They included children from grade 1 (6 years old) to grade 5 (10 years old) and had never benefited from any intervention in the field of PA. Schools were randomly assigned to either experimental (School A) or control group (School B; see Figure 1). Because the intervention is school based, all the children were included in the study (n=141 for school A and n=148 for school B). Based on studies already published on the same theme, the effects of the intervention are expected to be moderate (standard difference≈0.32, equivalent to an average change in MVPA measurement of 8 minutes per day; SD 18 minutes). In addition, in order to detect a difference of 0.32 with a statistical power of 0.8, a significance level of .05, and a retention rate of approximately 91% with a pre/post comparison, the number of participants should be 70. As a precaution, more children were included. Thus, the number of children enrolled was above the minimum required.

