### Statistical Analysis

STATISTICA version 12.5 (StatSoft/Dell) for Windows and R software will be used. Descriptive statistics of MVPA and ST for the whole day and within the different specific periods of the day will be calculated for both schools at the different assessment times. To examine the effectiveness of the intervention to promote PA and reduce ST, ANOVAs contrasting 2 schools × 5 assessment times with repeated measurement on the last factor will be used on MVPA and ST. Furthermore, chi-square analysis will be carried out to compare the number of children between experimental and control groups who comply with MVPA recommendations for the overall day and during school time.

To explore the longitudinal relationship between PA, motor skills, attention, and academic achievement, multiple regression analyses will be conducted to determine which variables will predict academic achievement scores [47]. We will attempt to examine whether PA or motor variables predict academic achievement through attention. As there are many variables in each category, a principal component analysis will be used to select the variables that are most correlated. Finally, the decision tree process will be used to examine more accurately the longitudinal relationships between the variables selected.

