In conclusion, physical inactivity and sedentary behavior are major public health problems. The implementation of this randomized controlled trial can help to determine effective strategies to promote PA in the context of increasing prevalence of physical inactivity among children with sedentary lifestyles. Understanding these strategies is a real necessity for researchers, stakeholders, and public policy makers seeking to establish health promotional actions for the population.

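### With one school per arm, the planned child-level tests can show that the two schools changed differently, not that the intervention caused it, and the article does not say so

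*Protocol article*

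**What the plan says.** The Abstract (Methods) reports that "1 school was randomly assigned as the experiment one and the other was assigned as the control one". Study Design and Population says that "The study was designed as a randomized controlled trial with 2 arms", with enrolment given as "n=141 for school A and n=148 for school B".

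The sample-size paragraph of that section counts children only. It uses a "standard difference≈0.32, equivalent to an average change in MVPA measurement of 8 minutes per day; SD 18 minutes" and "a statistical power of 0.8, a significance level of .05, and a retention rate of approximately 91% with a pre/post comparison", and arrives at 70 participants. It names no intracluster correlation, design effect or number of schools.

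Statistical Analysis plans that "ANOVAs contrasting 2 schools × 5 assessment times with repeated measurement on the last factor will be used on MVPA and ST", together with a chi-square comparison of how many children in each group meet the MVPA recommendation.

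T1 and T2 (2016/2017) precede the intervention year. T3 and T4 fall within it, and T5 follows a year later. The first aim is to evaluate effectiveness, and the Discussion concludes that "The implementation of this randomized controlled trial can help to determine effective strategies to promote PA". It does not list one school per arm as a limitation, and it presents the methodology as an improvement.

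**The concern.** School and intervention arm are the same variable in this design. A change of staff, timetable, canteen practice or intake in one school between 2016 and 2019 would appear in the data exactly as an intervention effect would.

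The planned tests judge the school contrast against variation between children. That variation says nothing about how much two untreated schools would drift apart. A small p-value would therefore be read as evidence of effectiveness when it shows only that the two schools differ in their course. This concerns the first objective of the study, and the effectiveness article is still to be written.

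**Working it through.** **1. The stated 70.** Inputs from Study Design and Population: d = 0.32, power 0.80, alpha 0.05, retention 91%, pre/post comparison.
- One-group paired formula, n = ((z_alpha + z_power)/d)². One-sided: ((1.645 + 0.842)/0.32)² gives 61, or 62 with the t distribution. Divided by 0.91 this is 68 or 69, close to 70.
- Two-sided paired: 77 or 79, inflated to 85 or 87.
- Two-arm comparison at d = 0.32, two-sided: 154 per arm before dropout.
- With d = 8/18 = 0.44 instead, a one-sided two-arm comparison gives 63, inflated to 70 per arm.

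The text does not settle which route was used. None of these formulas contains a cluster term.

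**2. Information at the level of randomisation.** Two schools minus two arms leaves 2 − 2 = 0 between-school degrees of freedom, so school-level variance cannot be estimated. Only two allocations were possible, so the smallest p-value from the randomisation itself is 1/2 one-sided or 2/2 = 1 two-sided. More children change neither figure.

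**3. What the baseline waves remove.** The school-by-time interaction compares change, so a constant difference between the schools cancels. A difference in change does not. The chi-square as described has no baseline term, so it lacks even the first protection.

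**4. Illustrative size.** Let s be the school-level share of the variance of the contrast analysed (for change over time, the school-by-time share), and m the children per school. A child-level test understates the standard error by a factor of √(1 + (m − 1)s), so

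true type I error = 2 × [1 − Φ(1.96 / √(1 + (m − 1)s))].

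Table 1 gives 45 and 51 children with accelerometry at T4, so m ≈ 48. A complete-case five-wave ANOVA could use no more than these. The values of s are assumptions.

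| s | 1 + 47s | 1.96 / root | True type I error |
|---|---|---|---|
| 0 | 1.000 | 1.960 | 5% |
| 0.001 | 1.047 | 1.916 | 5.5% |
| 0.005 | 1.235 | 1.764 | 8% |
| 0.01 | 1.470 | 1.617 | 11% |
| 0.02 | 1.940 | 1.407 | 16% |
| 0.05 | 3.350 | 1.071 | 28% |

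A slightly different variance convention, in which the naive variance contains only the within-school part, gives 11%, 16% and 30% for the last three rows. The formula is for a single contrast. For the full five-wave interaction it is only a guide.

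**5. In minutes.** With SD 18, s = 0.05 implies that two untreated schools would differ with an SD of √(2 × 0.05) × 18 = 5.7 min, against the 8-min target. SD 18 is itself insecure: 8 min at 0.32 implies 8/0.32 = 25, which would make it √0.10 × 25 = 7.9 min.

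**The case against.** The strongest reply is that the design has two pre-intervention waves and the planned ANOVA is longitudinal. A reader might infer from one school per arm that the whole school difference is confounded with the intervention. The documents do not support that: stable differences drop out of the school-by-time contrast, and only school-specific change stays aliased.

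The error rates are also open to challenge. No variance share is given, the share for change may be smaller than one for a single wave, and at 0.001 the inflation is trivial. Rates based on 100 or more children per school would overstate the problem for MVPA and ST, because post-baseline accelerometry numbers were 74 and 90 (T3), 45 and 51 (T4), and 71 and 86 (T5).

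A reader might also infer that the article hides its unit of allocation or already claims a causal result. It does neither. It says openly that schools were assigned, one to each arm. Its aim and conclusion are worded as an intention and a possibility, and it plans to replicate the intervention in the control school.

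These points limit the size and tone of the criticism. They do not answer it. Two schools cannot show that the share is zero, and an analysis plan that is not shown could not estimate a school random effect with one school per arm.

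**Conclusion.** The plan is wrong as written on this point. The ANOVA and chi-square p-values can show that the two schools changed differently. They cannot attribute that difference to the intervention, and the article does not acknowledge this.

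The structural part needs no assumption: there are zero between-school degrees of freedom, and the allocation supports no two-sided p-value below 1. The numerical part does. About 5.5% to 28% true error for a nominal 5% test holds for assumed shares of 0.001 to 0.05 at about 48 children per school, and the error is 5% only if the share is exactly zero. These figures illustrate the problem and do not estimate this trial's error rate.

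**What to change.** - Wherever the design is described, call it a two-school, cluster-allocated controlled before-after comparison with one school per arm.
- Report the between-school difference in change as an estimate, with an interval labelled as conditional on these two schools. Do not present child-level p-values as tests of effectiveness.
- Add a sensitivity table that widens the interval over assumed school-by-time SDs τ, with half-width 1.96 × √(SE² + 2τ²). As an example, take SD 18 and 48 children per school, so SE² = 18² × 2/48 = 13.5. The half-width is then 7.2 min at τ = 0, 9.1 min at τ = 2 and 13.2 min at τ = 4.
- Show the T1-to-T2 difference in change between schools as a descriptive check only. It is one realised drift, from November to June within one school year and mixed with season, so it cannot calibrate drift from year to year.
- State that the sample-size figure ignores clustering.
- Limit the conclusion to these two schools and list one school per arm as a limitation.

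This costs some wording and one table. No new data are needed, and the effectiveness article is still planned, so there is time. The downside is a weaker claim. A confirmatory test would need several schools per arm.

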**Results:**

The presented intervention and its different assessments have been successfully implemented. In order to achieve the 2 objectives of this randomized controlled trial, data analyses are about to be completed.

**Conclusions:**

The implementation of this randomized controlled trial can help to determine effective strategies to promote PA in the context of increasing prevalence of physical inactivity among children with sedentary lifestyle which will be useful for researchers, stakeholders, and public policy makers.

**Trial Registration:**

ClinicalTrials.gov NCT03983447; https://clinicaltrials.gov/ct2/show/NCT03983447

**International Registered Report Identifier (IRRID):**

RR1-10.2196/17815

## Introduction

### Background

Physical inactivity has been recognized in the last decade as a major cause of noncommunicable disease, being held responsible for more than 5.3 million of the 57 million deaths that occurred worldwide in 2008, and for a decrease in life expectancy [1]. Furthermore, physical activity (PA) has a protective effect against more than 20 chronic diseases, including obesity [2]. Thus, the World Health Organization (WHO) has set a global action plan to increase PA levels and decrease sedentary time (ST), with the aim of “a 15% relative reduction in the global prevalence of physical inactivity in adults and in adolescents by 2030” [3]. To reach that goal, primary school children are an important target because behaviors adopted in childhood affect health habits and lifestyle choices in adulthood [4,5]. International guidelines for 6-11-year-old children recommend at least 60 minutes of moderate-to-vigorous PA (MVPA) per day as well as a reduction of sedentary behavior [3]. However, data suggest that when conservative cut points are used to define MVPA, less than half of the children meet the 60-minute MVPA recommendation [6,7]. As an example, the IDEFICS study reported an average MVPA of 49 minutes for boys and 36 minutes for girls and an average ST of 370 minutes in 8-year-old children from 8 European countries [8]. Furthermore, children of low socioeconomic status seem to have lower PA levels as well as higher ST [9]. Thus, they should be specific targets for intervention because the WHO defines the reduction of inequalities as one of its Sustainable Development Goals [3].

Many studies have investigated the effectiveness of intervention programs for children to promote PA [10-12]. Given the fact that children spend a large part of the day at school, most of the interventions are carried out in this context [11-13]. This environment, dedicated to learning, allows the use of several actions and makes it possible to include children of any social class. Some interventions increase the frequency and duration of physical education classes and include health education workshops [14,15]. These workshops usually contain information on PA and nutrition. The results of these interventions are inconclusive because the children practice less PA outside of these extra physical education classes, leading to a reduced effectiveness [16,17]. In fact, school is not the only place for children to be physically active. The socioecological model of Sallis applied to health behavior identifies different levels of factors that influence children’s behavior, ranging from personal, interindividual (family or friends), community and environmental, and societal levels [18,19]. Some interventions act only on environmental factors, such as a new playground design adapted to PA practice. This type of environmental adaptation increased light PA and decreased ST, but did not affect MVPA [20]. Thus, as underlined recently by the WHO, a system-based approach should be favored, which means that interventions have to be integrated and multilevel to actually increase levels of PA and decrease ST [3]. In fact, there is strong evidence for the efficiency of school-based interventions with family and community involvement and multilevel interventions [16]. Thus, if actions are implemented at schools, workshops for parents and teachers should be added, especially in disadvantaged neighborhood that include many children from low socioeconomic status families [16,17].

As stated by the WHO, if PA has to be increased, ST also has to be reduced, and healthy PA habits should be learned during childhood [3-5]. In fact, if 7-year-old children spend about half of their waking time in sedentary behavior, this proportion increases up to around 75% at 15 years of age [21]. Furthermore, the effects of physical inactivity and sedentary lifestyle are independent of health, especially at the cardiometabolic level [22]. Thus, specific interventions to reduce ST are needed. Usually, these interventions focus on the development of classroom material. A literature review analyzed 13 studies and showed that height-adjustable desks decreased sitting time in the classroom [23]. Active classroom lessons are also used in several intervention programs to promote PA and break down ST, leading to improvement in on-task behavior during academic instruction [24]. In order to show evidence of the hypothesized change of behavior, an objective method of measurement of PA and ST, such as accelerometry, in preintervention and postintervention periods is necessary because self-reported ST is highly underestimated [25].

To help convince the educational authorities as well as the teachers to implement such interventions, recent evidence underlines the role of physical movement in the establishment of fundamental mental processes during childhood and adolescence, leading to cognitive benefits [26,27]. PA seems to have positive effects on the attentional capacities of children as well as academic achievement [28]. In fact, physical condition would be a mediatory element between PA and executive functions that include attentional capacities [29]. In addition, the development of gross and fine motor skills has a positive impact on cognitive capacities [30]. Thus, it is necessary to explore the relationships between PA, motors skills, attentional capacities, and academic achievement for children with low socioeconomic status.

### Aims

This article aims to present the rationale and methods for a randomized controlled trial among 6-10-year-old children with low socioeconomic status that will (1) evaluate the effectiveness of a school-based intervention designed to promote PA and reduce ST and (2) study the relationships between PA, ST, motor skills, attentional capacities, and academic achievement.

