#### Questionnaire

In addition to collecting academic achievement data, a questionnaire was distributed at the beginning of each school academic year (ie, T1, T3, and T5). Parents were asked to complete a questionnaire in order to obtain (1) sociodemographic information (age and gender of the child, socioeconomic data measured by the 4-item scale “Family Affluence Scale II” [FAS II] [46], marital status, and level of qualification of the parents) and (2) subjective information related to children’s PA and ST behavior (number of sports and outdoor activities practiced, parental perception of the competence of their children in PA practice, sedentary behavior of the child [time spent playing video games, watching television, and artistic and musical activities]).

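### The aims define the population by the child's own socioeconomic status, but selection is by school location, so inference is secured only at area level

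*Protocol article*

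**What the plan says.** The Aims, and the Objective in the Abstract in the same terms, announce "a randomized controlled trial among 6-10-year-old children with low socioeconomic status". Both objectives fall under that label: the effectiveness of the intervention, and the relations between activity, sedentary time, motor skills, attention and achievement.

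Study Design and Population describes a different rule of entry. It reports that "2 primary schools located in the city’s disadvantaged neighborhood were invited to participate in the study", and explains that in France "neighborhoods are classified as disadvantaged on the criterion of income per inhabitant", with the city and the country as comparators. It adds: "This defines the unfavorable social and economic conditions of the neighborhood and its inhabitants". As illustration it gives unemployment of 26% against 18% and social housing of 49% against 23%. It then states: "Because the intervention is school based, all the children were included in the study". Ethics Approval and Consent to Participate adds a signed parental form.

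The Questionnaire section lists "socioeconomic data measured by the 4-item scale" FAS II, together with parental qualification. Statistical Analysis names the school-by-time ANOVAs, the chi-square comparisons, and the regressions, principal component analysis and decision tree built on activity, motor skills, attention and achievement. It mentions no SES variable.

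**The concern.** The stated population is defined by a property of the child, while the rule of entry is a property of the neighbourhood. The two overlap but are not the same. A result averaged over all pupils of two schools could be read as an effect, or a relation, in low-SES children, although the design contains nothing that establishes each child's SES.

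The matter has more weight for the second objective. Those analyses are observational, so the allocation of schools gives them no protection. If family SES influences both how active a child is and how well the child does at school, a regression of achievement on activity, motor skills and attention will attribute part of the SES difference to activity.

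**Working it through.** The point concerns the definition of the population, so the first check sets the sections side by side. The arithmetic only shows how far FAS II could help.

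1. **Unit of definition.** Aims: the child's SES. Study Design and Population: area income, then whole schools. Consent is a further condition but not an SES criterion. No child or family threshold appears anywhere.

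2. **Do the two populations coincide?** The Background says that disadvantaged neighbourhoods include many children from low-SES families. Many is not all, and no share is given.

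3. **Wording elsewhere.** The Context section says the study focuses on children from disadvantaged neighbourhoods, and the Discussion restates the aims for disadvantaged primary school children. The article therefore names its population in two ways, and the Aims carry the one that the design does not secure.

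4. **Coverage of FAS II.** Input: questionnaire returns in Table 1. The T1 percentages reproduce: 90/142 = 63.4% (School A) and 113/168 = 67.3% (School B). Pooled:
   - T1: (90 + 113)/(142 + 168) = 203/310 = 65.5%, so 107/310 = 34.5% missing
   - T3: (60 + 73)/(135 + 154) = 133/289 = 46.0%
   - T5: (58 + 57)/(134 + 175) = 115/309 = 37.2%

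   These are upper limits, because a returned form may lack the FAS II items. Study Design and Population gives other school totals, 141 + 148 = 289. On that base, T1 coverage would be 203/289 = 70.2%.

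5. **Which FAS II value to use.** A T1 value cannot serve every child. Pupils in grades 1 and 2 at T5 (school year 2018/2019) would ordinarily not yet have been enrolled at T1 (2016/2017). The first available value per child is therefore needed.

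6. **Confounding in the second objective.** Suppose achievement depends on activity and on SES, with coefficient γ for SES, and let δ be the slope of SES on activity. Leaving SES out shifts the activity coefficient by γ × δ. The Background says that low-SES children seem less active and more sedentary, so δ is positive when higher SES is scored higher. If γ is also positive, which is an assumption, the shift makes activity look more favourable. The documents give neither γ nor δ, so the size cannot be stated.

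**The case against.** The strongest reply is that the area definition is disclosed. Study Design and Population states the criterion and supports it with comparative figures, and the Abstract's Background, the Context section and the Discussion already speak of disadvantaged neighbourhoods or disadvantaged children. Area income is a usable proxy for family SES. This stands. It means that inference is limited to the area level, not lost. A reader might infer that nothing about low-SES children follows from the trial; that is too strong, and the article's own Conclusions do not claim a result specific to them.

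A reader might also take the 49% social housing figure to mean that the other 51% of the area, and so perhaps half the pupils, are not low-SES. The documents do not support this. The figure describes the neighbourhood rather than the pupils, and living outside social housing does not mean that a family is not low-SES. Nor does the remark in the Background that the school setting "makes it possible to include children of any social class" describe this sample; it concerns school interventions in general. It is equally unsupported to put a number of minutes per day on the difference between the pooled MVPA effect and the effect in low-SES children. That needs a share and a difference in effect that the documents do not give, and the Background reports SES differences in activity levels, not in response to intervention.

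Finally, a condensed article need not list every covariate or baseline table, so the absence of FAS II from Statistical Analysis does not show that it will go unused. This also stands, and the mismatch between Aims and selection does not depend on it. The recommendation on the regressions rests on the predictors the article does name.

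**Conclusion.** The point holds as one of population definition, with a consequence for the second objective. The design secures inference for children attending primary schools in a disadvantaged neighbourhood; it does not secure it for individually low-SES children. The comparison between the two schools as such is unchanged, and no figure in the article becomes wrong.

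The practical size is unknown, because the share of low-SES pupils is not reported. What can be said is that FAS II describes at most 65.5% of children at T1 on the Table 1 denominators. The advice on the regressions assumes that family SES affects achievement as well as activity, and that it still varies within these two schools. If it varies little, adjustment will change little.

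Conclusions about low-SES children should not be moved to a low-FAS II subset. The documents give no cut-off for low, and the subset would be small and confined to families who returned the form.

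**What to change.** 1. In the Abstract's Objective and in the Aims, restate the population as children attending primary schools in a disadvantaged neighbourhood, in line with Context and Discussion.
2. Report the FAS II distribution by school, with the number missing (203 of 310 available at T1).
3. In the regressions of academic achievement, add family SES as a covariate: each child's first available FAS II, with parental qualification. Use multiple imputation for missing values and show the unadjusted result alongside. If a fuller analysis plan already contains this adjustment, it is enough to say so.

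The first two changes cost only wording and one descriptive table. The third uses data already collected. Its price is the missingness: with about 35% of FAS II values absent at T1, the analysis must either rely on an imputation model or drop those children and lose precision. The Results section says that the analyses are not yet completed, so all three changes can still precede the planned papers.
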